### EEG data collection and preprocessing

The EEG data will be collected with the AntNeuro EegoSport system, 64-electrode head cap at a sampling rate of 1024 Hz. The data will be downsampled to 200 Hz, high-pass filtered at 0.5 Hz, and low-pass filtered at 40 Hz using the Butterworth filter. The data will be epoched offline with a peri-stimulus window of − 100 to 400 ms, and baseline correction will be applied between − 100 and 0 ms. Next, artefact rejection will be performed by thresholding all channels at 100 uV and rejecting channels based on a 0.2-V threshold. We will then reference all the electrodes to the average reference. Finally, averaging will be conducted across all the trials. We will analyse event-related potentials from the onset of standard and oddball sounds, separately for stable and volatile conditions.

### Cognitive intervention-related changes in brain and behaviour: single-channel and behavioural analyses

To investigate if MMN improves after the compensation and adaptation therapy programmes, we will conduct a repeated measures 2 × 2 × 3 ANOVA design on mean ERP values, with MMN volatility (stable and volatile), treatment (CCT or CIRCuiTS), and visit (baseline, 12 and 24 weeks) as factors. Responders will be participants who make a clinically significant positive change based on the measures of cognition collected using Jacobson and Truax’s Reliable Change Index [22]. Mean ERP values will be obtained by averaging across the preselected time window of interest for MMN latency: 100–250 ms, over a frontocentral channel (Fz) [23]. In addition, we will investigate the behaviour, “regularity learning”, which is found to underlie the MMN response. We will conduct a separate repeated measures 2 × 2 × 3 ANOVA design with the following factors: regularity learning (stable and volatile), treatment (CCT or CIRCuiTS), and visit (baseline, 12 and 24 weeks). This behavioural analysis will be conducted to examine if the compensation and adaptation therapy programmes improve regularity learning ability. Significant interactions will be further analysed using paired *t* tests.

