### Sample size

In this equivalence study, we will focus on the primary outcome of cognition. We based our power analysis specifically on the BACS. We estimate a dropout rate of 15–20% (from treatment to 3-month follow-up) resulting in a final sample size of approximately 80 participants who will complete the study. This estimate is based on the dropout rates for studies with participants with serious mental illness as well as our experience with group randomised controlled trial research. Due to practicalities of group size and opportunities for running groups over the study timeframe, the maximum number of participants was set at one hundred.

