## Methods: data collection, management, and analysis

### Data collection and statistical methods

The primary efficacy analysis will assess average treatment group differences for the primary outcome measure BACS, over the entire study period (baseline, post-intervention, follow-up), and will use a likelihood based mixed-effects model, repeated measures (MMRM) approach. The MMRM model includes the fixed, categorical effects of treatment (CCT or CIRCuiTS), visit (baseline, 12 and 24 weeks), and treatment-by-visit interaction, as well as the continuous, fixed covariates of baseline score and baseline score-by-visit interaction. The MMRM includes all available data at each time point and is the preferred method of analysing clinical trial data in psychiatry as compared to more traditional repeated measures analysis of variance (ANOVA) and analysis of covariance (ANCOVA) models. Planned comparisons will be done with the MMRM models to determine between-group differences in change of symptoms measures from baseline to weeks 12 and 24. Results from the analysis of dichotomous data will be presented as proportions, with 95% confidence interval, and Fisher’s exact *p* value where appropriate. Non-parametric statistics will be used when assumptions for parametric methods are violated. Effect sizes will be calculated using Cohen’s guidelines. All tests of treatment effects will be conducted using a two-sided alpha level of 0.05 and 95% confidence intervals.

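### The MMN and regularity-learning ANOVAs are complete-case in their usual form, at odds with the protocol's own reason for preferring MMRM, and paired t tests cannot interpret an interaction involving treatment

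*Protocol article*

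**What the plan says.** The section on single-channel and behavioural analyses sets out "To investigate if MMN improves after the compensation and adaptation therapy programmes". It does so with a 2 × 2 × 3 repeated measures "ANOVA design on mean ERP values, with MMN volatility (stable and volatile), treatment (CCT or CIRCuiTS), and visit" at baseline, 12 and 24 weeks as factors. A second ANOVA of the same shape covers the behavioural outcome, with factors "regularity learning (stable and volatile), treatment (CCT or CIRCuiTS), and visit (baseline, 12 and 24 weeks"). The follow-up rule is the same for both: "Significant interactions will be further analysed using paired" t tests. The section gives no reason for choosing ANOVA and does not say how missing visits are handled.

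Three other statements bear on this:

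- Data collection and statistical methods specifies MMRM for one analysis: "The primary efficacy analysis will assess average treatment group differences for the primary outcome measure BACS".
- The same section justifies MMRM in general terms: "The MMRM includes all available data at each time point", and it "is the preferred method of analysing clinical trial data in psychiatry as compared to more traditional repeated measures analysis of variance (ANOVA") and ANCOVA.
- Sample size expects losses: "We estimate a dropout rate of 15–20% (from treatment to 3-month follow-up"), leaving about 80 of 100.

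**The concern.** There are two separate problems.

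**Lost data.** A classical repeated measures ANOVA over three visits needs all three from each participant. Someone with baseline and week-12 recordings who misses the 3-month visit would normally drop out of the whole analysis. Yet the Trial design section frames the MMN aim as change from baseline to post-treatment, which does not need the 3-month visit. The protocol prefers MMRM because it avoids this kind of loss, then uses the less favoured method here without explanation. Dropout may also be related to outcome: the Interventions section has the investigator withdraw participants whose mental state deteriorates to the point of admission, or whose capacity to consent is compromised.

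**Wrong follow-up test.** Each participant receives one treatment, so treatment is a between-person factor. A paired t test compares two measurements on the same people. If the treatment-by-visit or three-way interaction is significant, paired tests can only be run within an arm, or with the arms pooled. Neither estimates how much more one arm changed than the other. Run arm by arm, they invite the reading that a significant change in one arm and a non-significant one in the other shows a treatment difference. This problem remains even with no missing data.

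**Working it through.** **1. Inputs.** From the protocol: 100 participants, 1:1 allocation, 15–20% dropout, about 80 completers, two-sided alpha 0.05. It gives no SD, effect size or power for MMN or regularity learning, no split of dropout by visit, and no rate of unusable EEG. Anything needing those is marked as assumed.

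**2. The protocol's own figure.** Completers = N × (1 − d). 100 × (1 − 0.20) = 80, which matches the stated figure; 100 × (1 − 0.15) = 85. So a complete-case ANOVA analyses 80–85 and omits 15–20.

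**3. Unusable recordings (assumed).** If 5–10% of recordings per visit cannot be used, independently across visits, complete cases = 100 × (1 − d) × (1 − e)³. This runs from 85 × 0.95³ ≈ 73 down to 80 × 0.90³ ≈ 58.

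**4. Precision at week 12.**
- Assume 20 drop out and half of them give week-12 data. A mixed model has 90 at week 12 and the ANOVA has 80. Variance ratio 90/80 = 1.125. The mixed model's standard error is √(80/90) = 0.943 of the ANOVA's, about 6% smaller. At week 24 both have 80 observed.
- Upper bound, with all dropout after week 12: difference detectable at 80% power = (1.96 + 0.84) × √(2/n per arm). This gives 0.56 SD at n = 50, 0.61 at 42.5 and 0.63 at 40.

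**5. Completer bias (simulation, assumed inputs).** The set-up was 50 per arm, correlation 0.6 between visits, no true arm difference and 20% dropout in each arm, related to the week-12 value in one arm only. The complete-case estimate of the arm difference in week-12 change was off by −0.13 SD; the likelihood estimate was off by about −0.01. At week 24 both were off by about −0.01. The week-24 result reflects the equal-correlation assumption, under which selection on week 12 shifts baseline and week 24 alike.

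**6. Does the ANOVA compare the arms?** Yes. With 40 complete participants per arm and correlation 0.6, the simulated treatment-by-visit F test rejected in 5.5% of trials with no difference and in 88% with a 0.6 SD difference in change.

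**7. What paired tests can answer.**
- Visit, volatility, volatility by visit: within-person, so paired contrasts are suitable.
- Treatment by visit, treatment by volatility, and the three-way term: each contains a contrast between independent groups, so paired tests do not address it.

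**8. How often within-arm tests disagree when the arms do not differ.** With two independent arms and the same power p in each, P(exactly one significant) = 2p(1 − p). At p = 0.5 this is 2 × 0.5 × 0.5 = 0.50; at p = 0.8 it is 2 × 0.8 × 0.2 = 0.32. A simulation with 40 per arm, correlation 0.6 and equal true changes of 0.2, 0.3 and 0.45 SD gave 41%, 49% and 22%.

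**The case against.** A reader might infer that these analyses cannot compare the arms at all. The protocol does not support that: treatment is a factor in both ANOVAs, and the treatment-by-visit and three-way F tests are between-arm tests of change. The defect lies in the follow-up step alone.

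A reader might also call this a contradiction. It is not one. MMRM is specified for BACS, and nothing commits the EEG or behavioural analyses to it. But the stated preference is worded for psychiatry trial data generally, and no reason is given for departing from it. Unexplained inconsistency is the fair description.

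Other points on the plan's side:

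- No sentence says that participants with a missing visit are excluded. That follows from the usual form of the method, and an analysis plan not shown here could say otherwise. This stands as a caveat; the choice of ANOVA and paired tests is nevertheless written down.
- The stated aim, whether MMN improves, is largely within-person, and paired tests suit it. This stands. But the follow-up rule covers every significant interaction, and the design includes treatment.
- Reading significance in one arm only as an arm difference is a misuse the protocol does not propose. True, but no between-arm follow-up is offered in its place.
- The bias result needs dropout that differs by arm. Nothing in the protocol says that it will, or links withdrawal to MMN, and the stated withdrawal rule covers only part of the expected dropout. Material bias is possible, not shown.
- Sphericity, and treating baseline as a visit level, are not faults in themselves: standard corrections exist for the first, and the second is a legitimate way to test change.

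**Conclusion.** The point holds for two secondary analyses; the primary BACS analysis is untouched.

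- **Data loss.** About 15–20 of 100 participants would leave a complete-case ANOVA. That follows from the protocol's own dropout figure and the method's usual implementation. The cost in precision is modest: about 6% on the week-12 standard error under the half-of-dropouts assumption, and at most a rise in detectable difference from 0.56 to 0.61–0.63 SD. Unusable recordings would increase the loss by an amount the protocol does not allow one to estimate.
- **Follow-up.** This is the firmer of the two defects, since it does not depend on missing data. Paired t tests cannot interpret an interaction involving treatment. The 32–50% disagreement rate rests on an assumed 50–80% power per arm and equal true change.

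**What to change.** Replace both ANOVAs with a likelihood-based mixed model on all available recordings:

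- Responses at baseline, week 12 and week 24. Keep baseline as a response; as a covariate only, it would lose anyone without a usable baseline recording.
- Fixed effects for treatment, visit, volatility and all their interactions.
- An unstructured or similarly flexible within-participant covariance across visits and conditions. Fully unstructured, six measurements (3 visits × 2 conditions) need 6 × 7 / 2 = 21 parameters, so name a simpler fallback in case of non-convergence. A participant random intercept alone is not enough, because it imposes compound symmetry, which is stricter than sphericity.

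Replace the follow-up sentence. Any interaction involving treatment is followed by the between-arm contrast of change from baseline, with its 95% CI. Paired contrasts are kept for purely within-person effects (visit, volatility by visit). The protocol already plans between-group contrasts of change within its MMRM models, so this extends existing practice.

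The cost is a change of wording and slightly more modelling work. No new data are needed, and the model class is already planned for BACS.

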### Objectives

This study will use a randomised controlled trial to test the equivalence of CCT compared with CIRCuiTs to address the cognitive deficits of schizophrenia spectrum disorders. The primary objective is to examine the equivalence of CCT in improving neurocognitive deficits in people with schizophrenia spectrum disorders compared with CIRCuiTS. The secondary objective examines if CCT and/or CIRCuiTS are associated with objective and subjective improvement in community and cognitive functioning. In addition, we aim to determine whether MMN at baseline can be used to predict on an individual level, who might benefit from either treatment.

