### Trial design

The design is a single-blind, randomised controlled trial to examine the equivalence of CCT and CIRCuiTS. The trial also aims to examine if MMN at baseline can predict response to the compensation and adaptation therapies and if MMN improves from baseline to post-treatment.

The study will include 100 clinically stable patients with a schizophrenia spectrum disorder. Participants will be randomised in a 1:1 ratio to join either the CCT group or the CIRCuiTS group. Participants will all be active cases in Metro South Addiction and Mental Health Services (community based). Participants in the study will continue to receive standard clinical care (i.e. there are no restrictions on medication or psychosocial interventions, apart from participants receiving therapies addressing neurocognition). These two interventions will be delivered by trained mental health staff once (CCT 2-h session) or twice (CIRCuiTS 1-h sessions) per week for 12 weeks. Groups will be based on a maximum of 6 participants per facilitator. Individual clinical assessments will be at baseline, at post-treatment, and at 3-month follow-up. Randomisation will be carried out using a computer-generated randomisation table.

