### Outcomes

A battery of validated clinical measures will be conducted at baseline, at post-treatment, and at 3-month follow-up. Raters who are blind to the randomisation of condition (registered psychologists) will complete the measures. The assessors instruct the participant not to reveal their group allocation.

The following measures will be used:
Brief Assessment of Cognition in Schizophrenia (BACS) [17] is an instrument that assesses the aspects of cognition found to be most impaired and most strongly correlated with outcome in patients with schizophrenia. This is the primary outcome measure.Test of Premorbid Functioning (TOPF) [18] is a test of premorbid intelligence as estimated from reading ability.Subjective Scale to Investigate Cognition in Schizophrenia (SSTICS) [19]. This measures the perception of cognitive abilities when completing everyday tasks.Social Functioning Scale (SFS) [20] assesses areas of functioning that are crucial to the community maintenance of individuals with schizophrenia.Brief Psychiatric Rating Scale (BPRS) [21] is a widely used scale for measuring symptom severity of patients with schizophrenia.Electroencephalography (EEG). Participants will listen to a duration auditory oddball paradigm while their brain responses are measured with EEG. An auditory oddball paradigm consists of presentations of sequences of predictable sound stimuli (standard sounds) that are infrequently interrupted by unpredictable sound stimuli (deviant sounds). Sounds will be delivered via headphones and will vary in duration. All tones will be presented in a sound range that is comfortable for the participants. In the “volatility” auditory oddball task, the participants will be asked to pay attention to the sounds in order to judge the proportion of different sound types and rate their confidence on this judgement. This will allow us to assess the ability of participants to learn the statistical relationships of sound types, as well as the confidence on their own judgement. Prior to the experiment, the participants will be familiarised with the different sound types and trained with two short practice tasks. Participants will make responses using a computer keyboard and a mouse. The duration of the practice task will be 2 min, and the duration of the volatility auditory oddball task will be approximately 18 min, with a total duration of testing of approximately 20 min per participant, including breaks.

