### Predicting cognitive intervention response with machine learning: spatiotemporal maps and feature definition

To identify if EEG measures can be used to predict response to the compensation and adaptation therapies, we will use machine learning techniques to classify individual patients that benefit from the compensation and adaptation therapies (responders) from patients who do not improve after the compensation and adaptation therapies (non-responders). Machine learning will be implemented using the Pattern Recognition for Neuroimaging Toolbox (PRoNTo) [23] with features from the whole-brain spatiotemporal analysis. First, we will create three-dimensional spatiotemporal images from averaged ERP data. A three-dimensional matrix (32 × 32 × 81) corresponding to the scalp electrode space and time points will be constructed, per participant for the different conditions. The images will be smoothed at full width half maximum of 12 mm × 12 mm × 20 ms. Before conducting the machine learning, we will perform the standard spatiotemporal mass-univariate general linear model analysis. A full factorial analysis will be performed to examine the spatiotemporal changes after the therapy programmes, with the following factors: volatility (stable and volatile), treatment (CCT or CIRCuiTS), and visit (baseline, 12 and 24 weeks). All statistical maps will be thresholded at *p* < 0.05 family-wise error (FWE) corrected for multiple comparisons.

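### With two active arms and no untreated reference, change over visits and responder status show improvement during therapy, so the EEG models can predict who improves but not who benefits

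*Protocol article*

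**What the plan says.** Under Trial design, all participants receive one of two active therapies: "Participants will be randomised in a 1:1 ratio to join either the CCT group or the CIRCuiTS group". No arm is untreated, wait-listed or given usual care alone. Usual care continues, and "there are no restrictions on medication or psychosocial interventions, apart from participants receiving therapies addressing neurocognition". Testing is repeated: "A battery of validated clinical measures will be conducted at baseline, at post-treatment, and at 3-month follow-up" (Outcomes).

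The section on single-channel and behavioural analyses plans two repeated-measures ANOVAs, one on MMN and one on regularity learning. Each has volatility, treatment and visit as factors. Of the second it says: "This behavioural analysis will be conducted to examine if the compensation and adaptation therapy programmes improve regularity learning ability". Significant interactions are followed by paired *t* tests. The same section defines response: "Responders will be participants who make a clinically significant positive change based on the measures of cognition collected", using the Jacobson–Truax Reliable Change Index.

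The machine-learning section then sets out to "classify individual patients that benefit from the compensation and adaptation therapies (responders") and separate them from those who do not improve. Class labels cover both therapies together, and no treatment term is stated for the classifier. The kernel ridge regression is trained on BACS scores, and its accuracy is described as accuracy in predicting response to the therapies.

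The corresponding aim under Objectives reads: "we aim to determine whether MMN at baseline can be used to predict on an individual level, who might benefit from either treatment". The Discussion adds that clinicians will be able to identify people more likely to benefit from such a programme.

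**The concern.** Randomisation here identifies one thing: the difference between CCT and CIRCuiTS. It does not identify what either therapy does compared with no therapy. A visit effect, or a person's own change, contains the therapy effect plus whatever would have happened anyway: familiarity with a battery taken three times, medication changes, natural course and regression to the mean.

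Two readings in the plan go further. The behavioural ANOVA is said to test whether the programmes improve an ability, yet its visit effect is uncontrolled and its treatment-by-visit effect shows only which therapy changes more. The responder label is treated as benefit, so a classifier that predicts the label is presented as predicting benefit.

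Followed as written, the trial could report that therapy improved regularity learning, and that EEG predicts treatment benefit, when it had shown change over time and a prognostic association. The Discussion foresees use of the result in identifying people for therapy. The limitations listed there cover inter-rater reliability, unfinished CIRCuiTS stages and clinician effects, but not this.

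**Working it through.** **The plan's own figure.** Sample size gives 100 participants, 15–20% dropout and approximately 80 completers. 100 × (1 − 0.20) = 80 and 100 × (1 − 0.15) = 85, so 80 is the 20% end. Below I use 80 completers, 40 per arm.

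**Assumed inputs (not in the protocol).** Index cut-off 1.96 × SEdiff; retest reliability r = 0.7 to 0.9; non-therapy gain g = 0 to 0.4 baseline SD; normally distributed change.

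**Step 1: responders when therapy does nothing.** In baseline SD units, SEdiff = √(2(1 − r)), which is 0.775, 0.632 and 0.447 for r = 0.7, 0.8 and 0.9. The proportion labelled responders is 1 − Φ(1.96 − g/SEdiff). Counts out of 80 are in brackets.

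| Mean gain | r = 0.7 | r = 0.8 | r = 0.9 |
|---|---|---|---|
| 0 | 2.5% (2.0) | 2.5% (2.0) | 2.5% (2.0) |
| 0.2 | 4.4% (3.6) | 5.0% (4.0) | 6.5% (5.2) |
| 0.3 | 5.8% (4.6) | 6.9% (5.5) | 9.9% (7.9) |
| 0.4 | 7.4% (6.0) | 9.2% (7.4) | 14.3% (11.5) |
| 0.45, for comparison | 8.4% (6.7) | 10.6% (8.5) | 17.0% (13.6) |

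The last row takes the 0.45 effect size on global cognition from Background and rationale as if it were a mean change with no other gain. The first row shows that the index controls chance error whatever the reliability. The rows below it show that it does not remove a systematic gain. If improvement on either of two independent measures counted, the chance rate would be 1 − 0.975² = 4.9%.

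**Step 2: can a marker predict response when neither therapy works?** This was simulated with 400,000 participants and zero therapy effect. Change was g + b × marker + error, with the marker standardised and error SD equal to SEdiff.

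- b = 0, g = 0.2: AUC 0.50. A uniform gain alone does not make the marker predictive.
- b = 0.2, g = 0.2: AUC 0.68 (r = 0.8) and 0.73 (r = 0.9).
- b = 0.3, g = 0.3: AUC 0.74 (r = 0.8) and 0.79 (r = 0.9).
- Regression to the mean only, with the marker correlated 0.3 to 0.5 in size with baseline score (higher marker, lower score): AUC 0.55 to 0.61.

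An AUC above 0.5, or a significant permutation test, is therefore compatible with no benefit from either therapy.

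**Step 3: what the randomised arms could show.** For a baseline MMN-by-treatment contrast on change, with the marker standardised, the SE of the slope difference is √(1/40 + 1/40) = 0.224 residual SD. Power is about Φ(d/0.224 − 1.96), where d is the slope difference in residual SD per marker SD. It is 27%, 61%, 88% and 98% for d = 0.3, 0.5, 0.7 and 0.9. The contrast is estimable but weak unless the interaction is large.

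**The case against.** Several stronger readings are tempting, and the protocol does not support them.

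- **Measurement error is counted as benefit.** A reader might infer this from the responder definition. The same sentence names the Reliable Change Index, which exists to limit it. What remains is systematic gain. The article does not give the index's computation, and the full protocol may hold a practice adjustment; the point applies to the standard form.
- **The protocol promises to show who should get which therapy.** It does not. The Objectives speak of benefit from either treatment, and the other statements of the aim pool the therapies. A pooled label fits that aim; the difficulty is the word benefit.
- **The design rules out differential prediction.** It does not. The two randomised arms allow an MMN-by-treatment contrast, which is simply absent from the models described.
- **The trial needs an untreated arm, or its main result is biased.** Neither follows. Two active arms suit the stated aim ("The primary objective is to examine the equivalence of CCT in improving neurocognitive deficits"), and the primary BACS analysis compares randomised arms.

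It can also fairly be said that participants are clinically stable, medication changes are recorded, other cognition-directed therapy is excluded, and some wording is already neutral about cause. These reduce some alternative explanations but leave repeat testing and regression to the mean.

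The numbers have limits too. Reliability and gain are assumed. Above the 2.5% floor, a 0.3 SD gain adds only about half what a 0.45 SD effect adds. A false EEG signal also requires the marker to relate to non-therapy change or to baseline score. That is possible, but nothing in the protocol establishes it.

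**Conclusion.** The point stands as a fault of interpretation. The visit effects and the responder label cannot be attributed to therapy. The pooled classifier and the regression can show at most that EEG relates to who improves during therapy, which is less than the Objectives, the machine-learning section and the Discussion say.

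No single size can be given, because reliability and non-therapy gain are not in the protocol. Over a gain of 0.2–0.4 SD and reliability of 0.7–0.9, about 4–14% of completers (roughly 4 to 11 of 80) would be labelled responders with no therapy effect. An AUC of 0.68–0.79 could arise from a marker linked only to non-therapy gain.

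The primary between-arm BACS comparison is not affected, although finding the therapies equivalent would not by itself show that both work.

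**What to change.** 1. In the single-channel, behavioural and spatiotemporal analyses, interpret the visit effect as change over time. Attribute only the treatment-by-visit contrast to a difference between the therapies.
2. In the Objectives, the machine-learning section and the Discussion, describe the prediction result as predicting cognitive improvement during therapy. Report classifier performance by arm as well as pooled.
3. Add a separate exploratory BACS model containing baseline MMN (Fz, 100–250 ms), MMN-by-visit and MMN-by-treatment-by-visit, with the treatment and visit terms and the lower-order terms these imply. State that it is the only randomised evidence on differential benefit. Keep it outside the primary equivalence MMRM, where participants without baseline EEG could otherwise be lost.
4. Optionally, run a practice-adjusted index as a sensitivity analysis, but only if suitable external untreated retest data exist. The trial does not collect them.

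Items 1 to 3 use data already planned. The cost is a narrower claim, smaller numbers in the by-arm results, and an interaction test with low power (about 61% for a slope difference of 0.5 residual SD with 40 completers per arm, on the assumptions above).
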